### Intervention development

We conducted two intervention needs assessment and development projects preceding the cRCT described in this paper. The first was funded by VicHealth (2011-2014) and focused on job stress reduction in Victoria Police. This study included in-depth interviews (*n* = 13) and focus group discussions (*n* = 7) with Victoria Police members spanning a wide range of ranks: from Probationary Constables and Sergeants (station level) to Superintendents (region-wide responsibilities) and Commanders (organisation-wide responsibilities), as well as with OH&S, Police Psychology, and other member welfare departments. The details of this development project are described in a separate report [47]. In brief, the outcomes of relevance to this trial were a strong consensus across ranks on the need for improved supervisory support for junior officers, and a decision to develop and pilot a supportive leadership development and coaching program as a central element of the intervention in the trial. Access to guidance and support from senior members was frequently cited as a source of stress by junior members. High workload was also a salient theme, in particular report-writing, or ‘correspondence,’ was highlighted as a significant burden for junior officers. A specific intervention activity on workload management for junior officers was considered within the context of this trial, but was not included in the end due to resource constraints. As an alternative, workload management was a focus of leadership development and coaching for station command, with the intended outcome being that junior members would receive support and guidance in workload management through supervisory interactions with station command.

The second study was funded by Worksafe Victoria (2012–2013) and involved assessing member mental health literacy needs through additional interviews. A summary of relevant findings are provided below (details reported separately [48]. Five junior (probationary and confirmed and senior constables) and 13 senior (sergeant level and above) uniformed members participated in semi-structured interviews. The findings were combined with previous knowledge and understanding of the Victoria Police work context, including the other development project described above, and incorporated into recommendations for an integrated intervention strategy. Overall, this qualitative information suggested that senior members had better mental health literacy than junior members. Interviewees also identified stigma associated with mental health issues, and further, access to mental health literacy training varied widely across interviewees. Police members who felt they understood how to help someone with mental health problem reported learning these skills through their own life experiences (e.g. in the context of a family relationship), rather than through formal training. Members in leadership roles varied in terms of the degree to which others felt that they could be approached to discuss mental health issues. In addition, members preferred training via case studies, role plays and other mediums, rather than online. Lastly, a number of positive aspects of working at Victoria Police identified, such as meaningful work and camaraderie.

To ensure that our recommendations would be relevant, practical and feasible for Victoria Police, we consulted with seven Victoria Police subject matter experts chosen on the basis of their expertise or experience relating to one or more aspect of the intervention strategy. These included a senior Sergeant with an interest in staff welfare and peer support, a senior OH&S member, a representative from the Police Psychology Unit, two Inspectors with significant staff welfare portfolios, a senior peer support manager, and an Inspector with expertise in Sergeant and Senior Sergeant leadership training. These subject matter experts confirmed and validated the results regarding mental health literacy in Victoria Police, including the suggestions made by members for how to address mental health literacy gaps in this context (e.g., role plays and face-to-face contact rather than online training). They also offered constructive feedback and advice that enabled the intervention strategy to be refined and finalised in preparation for implementation in the trial. In particular, the integrated, station-level approach was seen as novel and promising, as the model drew on existing resources and aimed to deploy these in a more cohesive and sustainable manner. The subject matter experts also endorsed coaching as a way of developing and consolidating supportive management competencies that was compatible with the operational requirements of busy 24-hour stations. Finally, this group emphasised the importance of engaging with station leadership as early as possible and utilising a consultative approach to developing and managing the project.

### Intervention description

Following the in-depth intervention development and consultation process outlined above, it was agreed that we would test a station-level intervention aiming to make improvements in two main areas: psychosocial working conditions and mental health literacy. To the extent that improvements are achieved in these two proximal outcome areas, we would also anticipate improvements in the secondary outcomes of member mental health and organisational outcomes. The logic of the intervention--visually relating intervention activities, target groups, proximal outcomes, and secondary or distal outcomes—is presented in Fig. 2. The integrated and mutually-reinforcing nature of the various activities and outcomes should help to facilitate the desired changes in proximal and secondary outcomes. For example, improvements in supportive leadership should reduce job pressures for junior ranks as well as senior ranks (to the extent that they are better able to perform their roles), and parallel improvements in the mental health literacy should facilitate more open, two-way communication and problem-solving around job stress, distress related to factors outside of work, or combinations of the two. Such communication should enable action to identify and control job stressors and/or to seek additional help from internal sources or, where appropriate, health professionals. Furthermore, improvements in working relationships, particularly between junior ranks and supervisors, reinforced by expanded peer support activities, has the potential to improve mental health at all levels of the station hierarchy while also contributing to higher levels of organisational effectiveness.

**Fig. 2 Fig2:**
[figure not shown]
The logic of the intervention--visually relating intervention activities, target groups, proximal outcomes, and secondary or distal outcomes

The temporal flow of intervention activities at the station level is presented in Fig. 3. Activities include:

**Fig. 3 Fig3:**
[figure not shown]
Temporal flow of intervention activities at the station level. Activities include feedback of baseline survey results, a 360 ° leadership assessment for station leaders, the Creating Healthy Workplaces Leading for Wellbeing program for senior sergeants, sergeants and acting Sergeants, Victoria Police “Healthy Minds @ Work” program, peer support program within stations sites

*Feedback of baseline survey results*: Members of the research team will present a summary of station-level results to station leaders (those that have a supervisory role, specifically Senior Sergeants, Sergeants and Acting Sergeants) and junior ranking members (those that are below the rank of Sergeant, and do not have a supervisory role), via in-person presentation and posters, respectively. The presentations will be conducted by members of the research team who are degree-qualified at or above a Masters level in Organisation Psychology.*A 360° leadership assessment for station leaders:* This will be followed by a one-hour feedback and development session with a registered psychologist for each participating leader (tailored to their individual 360 assessment): The 360° leadership assessment was developed using the United Kingdom’s Health and Safety Executive’s management competencies for preventing and reducing stress at work, in combination with the Chartered Institute of Personnel and Development management competencies for enhancing employee engagement [49]. To complete the 360° leadership assessment, an individual leader will nominate one manager, five peers and seven direct reports to provide feedback on their leadership behaviours and competencies. Out of the five peers and seven direct reports, the research team will randomly choose three and five, respectively, to maintain respondents’ anonymity. The leader will complete the survey themselves, and their responses will be compared to others’. Once the minimum required number of responses are achieved, the leader will be debriefed by a registered organisational psychologist member of the research team, to explore the links between the individual’s leadership style, station culture and employee wellbeing outcomes, as measured by the baseline survey. Through the 360° debrief process, the leader will be guided to form one strength-based goal (e.g. being personally accessible and using that skill to have more conversations about wellbeing), and one developmental goal (e.g. having difficult conversations with staff in a more productive way).*The Creating Healthy Workplaces Leading for Wellbeing program for leaders (Senior Sergeants, Sergeants and Acting Sergeants):* This program is comprised of an initial five-hour workshop, followed by coaching sessions and concludes with a half-day follow-up workshop. The workshops will be run by members of the research team degree-qualified in psychology and trained in the coaching methodology being used. Workshops are provided to introduce leaders to the competencies that are necessary to ‘lead for wellbeing’, and to provide an opportunity to discuss what specific competencies (e.g., workload management) would look like in the context of law enforcement. The coaching sessions follow the initial one-day workshop and focus on the specific developmental needs of each participating leader as indicated by their 360° feedback. The coaching sessions will be conducted face-to-face, and one-on-one with individual leaders from the stations. Leaders will have a choice of who their coach will be: research team members, external professional coaches, and ‘peer coaches’ (sworn Police members who will be trained in the coaching methodology). Each leader will be offered four one-hour coaching sessions spanning 2–3 months, focusing on skill development specifically related to goals formed during the 360 debrief session.*Victoria Police “Healthy Minds @ Work” program*: This program was developed by registered psychologists within Victoria Police and provides information about common mental health problems such as depression and anxiety, as well as trauma, alcohol use and suicide. Two versions of the program are provided to stations. The first is a one-day leader training session that builds on leaders’ skills to have conversations with their members about such issues, and how to direct them to seek help. Another aim of the program is to decrease stigma around mental health issues and subsequently increase help seeking, both for the leaders themselves and their direct reports. The second is a two-hour mental health literacy session provided to all other ranks in stations. A research team member will attend the two-hour session to explain the relationship between “Healthy Minds @ Work” session and the overall Creating Healthy Workplaces program, so as to highlight that most of the intervention effort is dedicated to improving leaders’ people-management skills and enabling them to better support junior members.*Peer support program within stations sites*: We will make use of an existing peer support program to support and reinforce intervention activities and messages. Peer coaches will be briefed on intervention aims and activities, and will relay this information to peer support officers who operate within stations.

### Wait-list control sites

The same baseline and final assessments will be conducted at control and intervention sites. Victoria Police has committed to delivering a refined version of the intervention (including any changes or refinements indicated by effectiveness evaluation results) to control sites after study results are obtained. There will be no specific project-related intervention activities at control sites during the intervention period. However, control stations will not be prevented from implementing other workplace mental health activities for obvious ethical reasons. Any such activities occurring at control stations should be documented in our process evaluation, as detailed below. To the extent that such activities occur, we will attempt to adjust for them in analyses.

### Data collection

Baseline and follow-up data will be collected at 0 and 12 months respectively using an anonymous online iPad-Mini-based survey. This method was chosen in consultation with Victoria Police, and was informed by a number of considerations. First, identifying information is not usually requested in internal surveys (which average 20–25 % response), and when they do, respondents often leave the field/s blank. It was also anticipated that members would be especially reluctant to include identifying information on a survey that includes questions about mental health. Hence we decided to forgo the collection of identifying information, greatly limiting analysis possibilities, in order to optimise response rates and representativeness in the survey data. It was not possible to use incentives due to Victoria Police anti-corruption policies.

To further address concerns about confidentiality, we will use an electronic survey method that is independent of Victoria Police IT systems. The iPads are clearly marked as Deakin University property, and anonymity and independence from the host organisation’s IT systems will be emphasised in information sessions and promotion activities, alongside information on the voluntary nature of the survey on the welcome page. One or two iPads will be left at each participating station over a period of two to three weeks, during which time the number of responses will be monitored by the researchers on the university server to which the survey data is sent. Response rate updates will be sent to the station ‘champion’ who will help promote survey participation at the stations, and will be complemented by project field staff visits timed to coincide with shift changes to promote the survey.

Individual-level survey data will be complemented by station-level data collected from station command and relevant departments (e.g., HR), and will include staffing levels, changes in key staff at participating stations, restructures, and other events or activities that could affect intervention outcomes. Finally, qualitative interview data will also be collected as detailed below.

### Measures

The survey will contain a range of measures including the following.

#### Socio-demographics

Age group (categorical), sex, highest educational attainment.

#### Employment information

Current job title and rank, time in current position, length of employment in Victoria Police, full- versus part-time.

### Primary outcomes: Psychosocial working conditions and mental health literacy

#### Job control

A 9-item version of Karasek’s measure, including subscales of decision authority and skill discretion [50].

#### Job demands

An 8-item measure of quantitative and cognitive job demands [51].

#### Workplace social support

An 8- item measure including co-worker and supervisor, emotional, instrumental, appraisal and informational support [52].

#### Depression recognition

Will be measured using a written vignette featuring a 30-year-old man named ‘John’ [53, 54]. The vignette covers common symptoms of major depression with suicidal features and meets both Diagnostic and Statistical Manual for Mental Disorders, fourth edition (DSM-IV) and International Classification of Disorders, tenth edition (ICD-10) criteria for this condition [55, 56]. Respondents are asked for an open-ended response to identify what problem, if any, John has.

#### Willingness to assist

The depression vignette is followed by a question asking the respondent if they would help John if he was a co-worker; if yes, the respondent is asked whether the help offered would include any of a list of 6 actions (e.g., suggested they talk to health professional). The respondent is then asked about their degree of confidence in having a conversation with someone at work with a problem like John’s.

#### Personal depression stigma

A measure of stigmatising attitudes towards John as a hypothetical colleague with depression will be assessed using the first six items on the personal subscale of the Depression Stigma Scale [57]. These items assess the degree to which respondents perceived that a person with depression can ‘snap out’ of the problem if they wanted, that depression is a sign of personal weakness, that depression is not a genuine medical illness, and that persons with depression should be avoided as they are contagious, unpredictable, or dangerous.

#### Beliefs about treatment

The vignette is also used as reference to ask the respondent their view on the degree to which various sources of help might helpful or harmful (e.g., seeing their GP, dealing with problem on his own, etc.) [54].

#### Recent helping behaviours

Respondents will be asked to indicate (yes/no/don’t know) whether, over the past six months, they have worked with a colleague suffering from a mental health problem, and if yes, whether they tried to help that person, and if yes, in what ways (six choices, for example: suggesting they see a health professional, plus an open-ended ‘other’) [18].

#### Recent help-seeking behaviours

Respondents are asked “in the past 6 months, if you had a mental health issue, did you seek professional help?,” with response options yes/no/haven’t had an issue. If yes, respondents were asked to indicate the type of help sought (seven choices, e.g., a psychologist, police union, etc.).

#### Help-seeking intentions

Respondents will be asked if they were to experience a mental health issue in the future, how likely they would be to seek help from each of 13 sources (response options on 5-point Likert scale).

#### Help preferences for workplace stress

Respondents will be asked: if they were experiencing workplace stress, how likely they would be to seek help from peers and managers (response options on 5-point Likert scale).

#### Managers’ mental health knowledge, skills and stigma

Respondents at Sergeant rank or higher (only) will be presented with a set of 12 statements on attitudes and behaviours towards employees with mental health problems, gauging their degree of agreement or disagreement on a 6-item Likert-scale [58, 59].

### Secondary outcomes: Mental health & wellbeing, and organisational outcomes

#### Job tension index

A six-item measure of work-related tension and stress [60].

#### Psychological distress

Kessler 6-item measure of psychological distress [61].

#### Job satisfaction

A 14-item measure including subscales of intrinsic and extrinsic job satisfaction [62].

#### Station-level sickness absence rate

Obtained from Victoria Police HR as the average per full-time equivalent (FTE) over six months by station. The validity of this data will be checked by collecting station-reported FTE and comparing this to centrally-provided estimates from HR.

#### Organizational cynicism

A 5-item measure adapted for use in Victoria Police [63] was used to measure employee cynicism towards the willingness and/or capacity of the organisation and its leaders to follow through on promises and to achieve stated goals.

#### Organisational depression disclosure norms

Perceived organisational depression disclosure norms within Victoria Police was measured using four items adapted from Martin et al. [64] (1) *Employees in Victoria Police would be hesitant to disclose that they were suffering from depression*; (2) *In Victoria Police, you should not tell anyone if you have depression*; (3) *Employee depression is considered a suitable topic for discussion in Victoria Police*; (4) *In Victoria Police, your career would be over if you told anyone that you were suffering from depression*. Response options on a 6-point rating scale ranging from ‘1’ (strongly disagree) to ‘6’ (strongly agree).

### Process evaluation

A process evaluation will be conducted to provide narrative insight into the implementation of the intervention. Intervention staff will be asked to record field notes following every intervention activity (noting activity type, where [which cluster], duration, with whom, how many in attendance, etc.) as well as their experiences and impressions following the activity. This will allow for combined collection of quantitative and qualitative process data. Explicit description of the intervention and research process allows for reflexivity among the intervention field staff and will inform data analysis and effectiveness evaluation [65, 66]. Field notes will also be collected following data collection at control stations, with particular attention to workplace mental health-related activities that might occur independently of the project activities.

Semi-structured interviews will also be conducted by a project qualitative researcher with intervention field staff, key project personnel and selected key informants at Victoria Police intervention and control sites as well as some other parts of the organisation (e.g., to identify intervention-independent activities or occurrences that may affect outcomes). The qualitative researcher has extensive experience in conducting interviews and focus group discussions as well as qualitative data analysis.

Focus group discussions will also be conducted with Victoria Police participants at each intervention station after the final intervention workshops. Interviews and focus group discussions will aim to gain insight into (whether and) how the intervention is being, or was, implemented, and how it is being, or was, received at the site/station. The combination of qualitative and quantitative methods outlined for this intervention will enable exploration of pre-existing context-specific factors that may modify intervention effectiveness [67]. This is especially important for this study due to the intervention being implemented in four temporally-staggered sets of 3 stations (each sets of 6 stations is randomised to 3 intervention and 3 control stations) over varying locations. These findings will be used for formative evaluation purposes, referring to the use of these findings to make changes to, or fine tune local intervention activities and strategies.

#### Qualitative analysis

Interviews will be audio taped, transcribed and analysed thematically using *NVivo* for Windows along with intervention staff field notes to describe the evolution of the intervention and what the intervention ‘looked like’ at completion [68]. These analyses will be complemented by the quantitative process data described above to provide a detailed description of intervention implementation across clusters and over time. The quantitative post-intervention survey (described below) will also include questions about participation in specific types of intervention activities to provide measures of intervention reach or penetration (i.e., comparative levels of participation in activities) overall and by cluster.

### Analysis

The following main hypotheses on intervention effectiveness will be tested comparing the intervention versus the control sites at the cluster level based on cluster-wide survey responses:There will be significantly greater improvement in the intervention compared to wait-list control arms in the primary outcomes of mental health literacy and psychosocial working conditions over a one year period;There will be significantly greater improvement in the intervention versus control arms in the secondary outcomes of mental health and organisational outcomes over a one year period;

Analyses will be conducted following CONSORT guidelines for cluster-randomised trials [69]. Because we are not collecting individual identifier information, within-person analyses over time are not possible. A simple two-stage analysis approach will be used: summary measures (e.g., means) will be generated by cluster for pre- and post-intervention, and pre- and post-intervention values will be subtracted to give the mean change by cluster, followed by a two-sample test comparing the summary measures by arm (e.g., t-test, where *n* = total number of clusters). Cluster summaries will be based on census surveys within each station, with all respondents included regardless of whether they participating in intervention activities or not. We will additionally adjust for variation in cluster (station) size by weighting by the number of individuals per cluster. Pending the results of process evaluation, further analyses may be conducted to explore the influence of intervention fidelity and reach, or to attempt to account for activities at control stations that may have influenced outcomes.

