### Power and sample size

Sample size was calculated taking into account the cluster design (Table 1). Effect size estimates for mental health literacy outcomes were based on observed significant changes in the primary outcome of mental health knowledge in previous randomised, controlled intervention studies [18, 20]. This is based on a scaled ‘quiz’ score and was the best available measure of workplace mental health literacy. We estimated effect size for changes in psychosocial working conditions based on previous studies [70–72], taking into account distributional methods (which often estimate minimally important score differences as ~0.5 standard deviations [73]) plus the amount of apparent change that is likely attributable to measurement error (based on test-retest correlations over a short period of time [71, 72]).

**Table 1 Tab1:** Sample size and power calculations for mental health literacy outcomes evaluated in this randomised controlled trial taking into account the cluster design at Alpha = 0.05 and Power = 0.90

	Mean	SD	Effect size (d)	Req’d standard sample size N	ICC	Design effect	Required sample size accounting for cluster design N	Required sample size after allowing for 30 % attrition
Mental health knowledge (*n* = 423)	11.14	3.57	1.79	84	0.050	1.95	164	234
Job control (*n* = 678)	49.82	11.02	8.0	40	0.032	1.60	64	91
Psychological demands (*n* = 700)	14.85	3.73	3.9	20	0.050	1.94	39	56
Colleague social support (*n* = 712)	3.07	1.23	1.2	23	0.048	1.92	44	63
Supervisor social support (*n* = 710)	3.10	1.38	1.4	21	0.019	1.37	29	41

Cluster size was set at 20 based on the rule of thumb for cluster size of m <1/ICC, assuming average ICC ~0.05 (consistent with observed values in Table 1). The ICC was used to calculate the Design Effect sample size multiplier = 1 + (m-1)(ICC). The resulting sample size estimate was then further inflated to allow for 30 % attrition at final. The cluster size of 20 is conservative, representing the minimum size for inclusion. Many clusters/stations will likely exceed this size, thus allowing for less than 100 % recruitment into the study at baseline. Resulting sample size estimates for the intervention arm are presented in the far right column of Table 1. Based on the proxy mental health literacy outcome, we will recruit 12 clusters of >= 20 participants into each arm of the trial (n of 234/20 = 11.7, or 12 clusters per arm).

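### Twelve measures are labelled primary with no key measure, composite or success rule, so the stated alpha of 0.05 and power of 0.90 do not describe the primary hypothesis

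*Protocol article*

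**What the plan says.** The hypothesis appears in the Background and again under Analysis: "significantly greater improvement in the intervention compared to wait-list control arms in the primary outcomes of mental health literacy and psychosocial working conditions". The heading in the Measures part of the protocol article is "Primary outcomes: Psychosocial working conditions and mental health literacy", and twelve headed measures follow it before the secondary outcomes begin.

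- **Working conditions (3):** job control, job demands, workplace social support.
- **Mental health literacy (9):** depression recognition, willingness to assist, personal depression stigma, beliefs about treatment, recent helping behaviours, recent help-seeking behaviours, help-seeking intentions, help preferences for workplace stress, and managers' knowledge, skills and stigma.

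Several of these have parts. Job control is described as "including subscales of decision authority and skill discretion", social support as "including co-worker and supervisor, emotional, instrumental, appraisal and informational support", and help-seeking intentions are rated for 13 sources. One is asked of a subgroup only: "Respondents at Sergeant rank or higher (only) will be presented with a set of 12 statements". The two recent-behaviour measures apply only to respondents who had a colleague with a problem, or had one themselves.

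Table 1 is headed "taking into account the cluster design at Alpha = 0.05 and Power = 0.90". It has five rows: a knowledge score, job control, demands, colleague support and supervisor support. The knowledge score sets the trial's size. The Power section calls it a proxy, and it is not one of the twelve listed measures. The Analysis section describes a two-sample test on station mean changes. It gives no significance level per test and no rule for how many measures must succeed.

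**The concern.** A primary hypothesis over a set of measures has an error rate and a power only once the plan says what counts as success. Here the set is fixed and the rule is not. If any one measure is enough, the chance of a false claim is well above the stated level. If every measure must succeed, error is controlled but power is not 0.90.

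The stake is practical. The abstract says that positive results would lead to adaptation across an organisation of about 16,500 employees. What makes the primary result positive is not defined.

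**Working it through.** **Inputs from the protocol.** Two-sided 0.05 (sidedness is not stated, but two-sided reproduces the table); power 0.90; 12 stations per arm, so 22 df for an unweighted t-test; for the knowledge row, difference 1.79, SD 3.57, ICC 0.050, cluster size 20, attrition 30%.

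**Assumed.** A common correlation ρ between the twelve station-level outcomes. The protocol gives none, so a range is shown.

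**1. Reproduce Table 1 (knowledge row).**
- n per arm = 2(1.960 + 1.282)² × (3.57/1.79)² ≈ 83.6, so 84.
- Design effect = 1 + 19 × 0.050 = 1.95; 84 × 1.95 = 163.8, so 164.
- 164/0.70 = 234.3, so 234; 234/20 = 11.7, so 12 stations per arm.

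The other four rows also reproduce: 40, 20, 23 and 21 per arm before clustering, and 91, 56, 63 and 41 at the end. Each row therefore uses the whole 0.05.

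**2. If one significant measure is enough.** For independent tests:
- any false positive: 1 − 0.95¹² = 0.460;
- any false positive favouring the intervention: 1 − 0.975¹² = 0.262.

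For correlated outcomes, twelve t-tests were simulated on 12 v 12 stations with no true effect:

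| ρ | At least one p < 0.05, either direction | At least one favouring the intervention |
|---|---|---|
| 0 | 46% | 26% |
| 0.3 | 40% | 21% |
| 0.5 | 33% | 16% |
| 0.7 | 24% | 12% |

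The nominal figures for a single test are 5% and 2.5%. Testing parts of measures separately would raise the number of tests above twelve.

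**3. If all twelve must succeed.** Suppose each really had power 0.90. Joint power is then 0.90¹² = 0.28 if independent, about 0.57 at ρ = 0.5 and about 0.67 at ρ = 0.7 (normal approximation). Even the premise is untested for the nine literacy measures, since none has a row in Table 1.

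**4. If a correction over twelve were added later.** Bonferroni gives 0.05/12 = 0.0042 per test. On Table 1's own method the knowledge row then needs 137 per arm before clustering. 137 × 1.95/0.70 = 381.6, and 381.6/20 = 19.1, so 20 stations per arm. With the planned 164 analysed per arm, power drops from 0.90 to about 0.65.

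**The case against.** The strongest reply is that the protocol nowhere says each measure will be tested at 0.05. That level is a sample-size input, the Analysis section is silent, and a statistical analysis plan may exist that sets an adjustment. This stands as far as it goes: the error rates above are conditional. It does not remove the point, because the set of primary measures and the sample size are both fixed here. Step 4 shows that a correction over all twelve would not fit that sample size.

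A second reply is that the hypothesis is directional, so results favouring control cannot confirm it. That is right. The 12–26% column is the one that matches a false claim of benefit, and the 24–46% column overstates that particular harm about twofold.

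Three stronger readings are tempting and are not supported:

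- A reader might infer that one p < 0.05 confirms the hypothesis. No such rule is written, and the wording joins the two domains with an 'and'. A rule requiring both domains or all measures would shrink or remove the inflation and turn the problem into one of power.
- A reader might take 33–46% as the range. Its lower end needs a correlation of 0.5 that the protocol does not give, and it is not a floor.
- A reader might put a power figure on the managers-only measure. That needs the number of responding managers per station and a station autocorrelation, and the protocol gives neither.

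**Conclusion.** The point holds in a conditional form. What is certain from the text is that twelve measures are primary, none leads, there is no composite or success rule, and 0.05 is the only level given and is spent in full on each Table 1 row. Neither an any-measure nor an all-measures reading is described by the stated 0.05 and 0.90.

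The size depends on two assumptions: that each measure is tested at two-sided 0.05, and the correlation between outcomes. Across the range shown, the chance of a false result favouring the intervention is about 5 to 10 times the nominal 2.5%. Confidence is high on the labelling and lower on the exact rate. This is a primary set fixed badly in the protocol, not a detail left to a later plan, and it should be corrected.

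**What to change.** Before any comparative analysis:

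1. Name one primary measure, or one composite with its scoring fixed in advance, for each domain. Choose from measures collected from all ranks. Supervisor support is one candidate for working conditions, since supportive leadership is central to the intervention; other choices would also close the gap.
2. Test the two with Holm, or at 0.025 each.
3. Move the remaining measures to secondary and report them with confidence intervals. This includes the managers-only measure and those answered only by respondents routed to them.
4. Restate Table 1 for the named measures at the alpha actually used.

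**Cost.** The change is to protocol and registry wording, with no new data. Trial status reports only the first of four strata at follow-up, so there was time to make it.

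Stated power falls. On Table 1's terms, 0.025 raises the knowledge row from 84 to 99 per arm; 99 × 1.95/0.70 = 275.8, or 13.8 stations of 20, against the planned 12.

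On the planned change score, assume a 0.5 SD effect, ICC 0.05 and station autocorrelation 0.8 (the last is not in the protocol). The variance of a station's change is 2 × 0.05 × (1 − 0.8) + 0.95 × (1/m₀ + 1/m₁), where m₀ and m₁ are respondents per station at baseline and follow-up.

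- **14 at both surveys:** 0.020 + 0.136 = 0.156; standard error of the arm difference √(0.156 × 2/12) = 0.161; 0.5/0.161 = 3.10. Power with 22 df is about 0.84 at 0.05 and 0.75 at 0.025.
- **20 at baseline, 14 at follow-up:** variance 0.135, standard error 0.150, ratio 3.33. Power at 0.025 is about 0.81.

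These are the figures for the stricter 0.025 split. Under Holm, the second measure is tested at 0.05 once the first has succeeded, so the loss is somewhat smaller.
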